### Intervention

#### Intervention group (IG)

The intervention condition is a structured psycho-oncological intervention based on the Managing Cancer And Living Meaningfully (CALM) manual. CALM is an individualized, evidence-based psychotherapeutic intervention that focuses on four domains relevant to the challenges typically experienced by cancer patients:Symptom management and communication with healthcare providersChanges in self and relations with close othersSpiritual well-being and a sense of purposeConcerns related to the future and mortality [28]

The topics covered in the CALM domains are also relevant for relatives. Adaptations of the intervention therefore refer to the fact that in all domains, the well-being (e.g., physical and psychological symptoms) and the self-perception of the relative (e.g., change in values since the relative’s illness) are explored instead of the well-being and perception of the patient.

The CALM domains should be addressed in a tailored, individualized manner that allows for variation in time spent on each domain and the number of sessions based on the participants’ needs. Therefore, each relative receives three to six counseling sessions, each lasting 45 min. A CALM-trained psychologist delivers the sessions within 6 weeks. Three psychologists of the CCCMF (experienced psycho-oncologists/psychotherapists) were trained to do the CALM intervention at the psycho-oncological department.

#### Control group (CG)

Relatives of the CG receive written information about the offers (e.g., counseling, relaxation groups) of psycho-oncological care at the CCCMF by giving the patient the information flyer of the psycho-oncological department. This offer of psycho-oncological care with single and group interventions for patients and relatives corresponds to usual care. Therefore, psycho-oncological counseling is also possible in the CG but is based on personal needs and active engagement. This needs-based counseling in usual care is not structured according to the CALM approach. Furthermore, it is not standard to schedule as many counseling sessions within 6 weeks. This control condition was chosen for ethical reasons.

No specific psycho-oncological intervention is proactively offered to the lung cancer patients in both study arms. However, they can request the support of the psycho-oncological team of the CCCMF (usual care).

#### Treatment integrity

We document the number of counseling sessions in both study groups. As mentioned, there is no restriction for other (psycho-oncological) treatments or counseling.

### Outcomes and measurements

The primary outcome is anxiety. Secondary outcomes are depression and distress for both relatives and patients, supportive care needs, and quality of life for relatives. All outcomes are assessed using self-report validated questionnaires. In addition, sociodemographic data are collected by self-report and medical data by the medical record. Table 2 presents an overview of outcomes and assessments.

**Table 2 Tab2:** Outcomes, measures, and assessments

Outcomes	Measures	Items	Assessment			
			**Relatives**		**Patients**	
		***n***	**T0**	**T1**	**T0**	**T1**
Anxiety	Generalized Anxiety Disorder-7 Questionnaire (GAD-7) [29]	7	X	X	X	X
Depression	Patient Health Questionnaire-9 (PHQ-9) [30]	9	X	X	X	X
Distress	Distress Thermometer (DT) [31]	1	X	X	X	X
Unmet needs	Supportive Care Needs Survey (SNCS) [32]	34	X	X	–	–
Quality of life	Caregiver Quality of Life Index-Cancer (CQOLC) [33]	35	X	X	–	–
**Further variables**						
Sociodemographic data	Gender, age, education level, relationship to family member/patient, previous psychological treatment	5	X	–	X	–
Medical data	Date of diagnosis, histological subtype, UICC tumor stage, smoking	4	–	–	X	–
Treatment integrity	Number of counseling sessions	1	–	X	–	X

*T0* baseline, *T1* after intervention/6 weeks, *UICC* Union for International Cancer Control

#### Anxiety

The Generalized Anxiety Disorder-7 questionnaire (GAD-7) is a valid and reliable short instrument for assessing symptoms of a generalized anxiety disorder based on the diagnostic criteria of the DSM IV [29, 30]. Seven items record the frequency of anxiety symptoms in the last two weeks using a 4-point Likert (0 = not at all; 1 = several days; 2 = more than half of the days; 3 = nearly every day). Items are summed up to a score ranging from 0 to 21, with higher values indicating higher anxiety [29]. The GAD-7 is particularly useful for assessing the severity of anxious symptomatic and monitoring changes over time [30].

#### Depression

The Patient Health Questionnaire-9 (PHQ-9) assesses the severity of depressive symptoms in the past 2 weeks [31]. The questionnaire consists of nine items derived from the DSM IV/DSM V diagnostic criteria and has high content validity [32]. The items are scored on a 4-point Likert scale (0 = not at all; 1 = several days; 2 = more than half of the days; 3 = nearly every day). The sum score may range from 0 to 27, with higher values indicating higher depression [31].

#### Distress

The Distress Thermometer is a simple and sensitive screening tool to assess psychosocial stress in oncology patients [33, 34]. It assesses distress within the last week on an 11-point rating scale from 0 (not at all stressed) to 10 (extremely stressed). A cutoff value of 5 or more indicates high distress and need for support [33].

#### Unmet needs

The short form of the Supportive Care Needs Survey (SNCS) [35] measures the nature and extent of the perceived needs of oncological patients with 34 items in 5 dimensions: health care system and information; psychosocial well-being; physical well-being; daily living, patient care, and support; and sexuality. On a 5-point Likert scale, patients indicate whether and to which extent they need support (0 = no need, not applicable; 1 = no need anymore, already have support; 2 = low need; 3 = moderate need; 4 = high need) [36]. A standardized value between 0 and 100 and an adjusted value can be calculated [37].

#### Quality of life

The Caregiver Quality of Life Index-Cancer (CQOLC) is used to assess the quality of life of the relatives of cancer patients. The CQOLC is a valid and reliable questionnaire that measures cancer’s psychosocial effects on relatives using 35 items. Several statements regarding how they have felt in the last few days must be rated on a 5-point Likert scale (0 = not at all; 1 = a little; 2 = somewhat; 3 = quite; 4 = very much) [38]. A higher total score (range 0–140) indicates a better health-related quality of life.

For the primary and secondary outcomes, differences between the IG and CG at T1 will be assessed using aggregated questionnaire scores (mean values).

### Sample size calculation

A recent systematic review of interventions for relatives of cancer patients with partly different tumor entities showed heterogeneous results. Many of the included studies showed nonsignificant improvements in outcomes due to insufficient power [25]. Following previous intervention studies with this patient group, which focus on the support of relatives, an effect size of *d* = 0.4 is set [25]. To demonstrate an effect of *d* = 0.4 in the primary outcome (GAD-7) at a significance level of alpha = 0.05 and beta = 0.2 for comparing two independent samples, *n* = 200 relatives are required (100 per group). Due to heterogeneous results and high effort in recruiting this vulnerable group, we plan an interim analysis with *n* = 88 persons (44 per group; sample size showing a medium effect size *d* = 0.6). The trial will be closed if the effect size is *d* = 0.6 or *d* < 0.4. A member of the statistical consulting of the Institute of Clinical Epidemiology, University of Würzburg, supported sample size calculation.

### Recruitment

Lung cancer patients treated in the University Hospital Würzburg and their relatives are recruited either in the pneumatological outpatient clinic or by contacting the patients or their relatives by phone. Eligible persons are informed about all relevant aspects of the study, i.e., the psycho-oncological intervention for the relatives, the procedure, and assessments. It is also explained that participation in the study is voluntary and can be terminated at any time without giving a reason. In the case the patients and their relatives are interested in the study, they get written study information, a flyer with the offers of the psycho-oncological department of the CCCMF, the baseline set of questionnaires (T0), and an informed consent form (in person or delivered by mail). After written consent is provided and the initial questionnaires (T0) are completed, a psycho-oncologist will contact relatives in the IG to set a date for an initial appointment, whereas CG will not be actively contacted.

### Assignment of interventions

#### Randomization and allocation concealment

All participants, i.e., dyads of relatives and lung cancer patients, will be randomly assigned to IG or CG after consent is given and initial questionnaires (T0) are completed.

A block randomization procedure with an allocation ratio of 1:1 is used. A member of the study center (not involved in the study) created the randomization list with computer-generated random numbers linked to the research codes (i.e., a consecutive list of numbers). The research code is used on all questionnaires and medical data instead of the name (pseudonymization; see confidentiality). The list is stored locked at the study center. Research codes are printed on the first questionnaires (T0). Therefore, assignment based on the sequence of the list is determined by the time of receipt of the interest to participate and, consequently, the distribution of the study information, consent form, and questionnaire. Allocation concealment will be ensured, as the study members responsible for enrollment (i.e., study coordinator) will not release the randomization number until the signed consent form and baseline assessments have been completed.

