#### Blinding

Blinding of participants and psycho-oncologists is not possible due to the active counseling intervention. However, psycho-oncologists are not involved in recruitment and data collection. Other care providers are blind to study participation and/or assignment. For organizational reasons, the analysts will not be blinded. The members of the study team will each take on several tasks. They are responsible for enrollment, data collection, management, and statistical analysis.

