### Data collection, data management, confidentiality, and retention

Data will be assessed with patient questionnaires (paper–pencil), and medical data will be extracted from the medical record. The baseline set of questionnaires (T0) will be administered in person or delivered by mail. The follow-up questionnaires (T1) will be sent by mail with a prepaid envelope for return. Researchers will check the responses and, if necessary, contact nonresponders via telephone to promote complete follow-up.

All data will be transferred manually to a statistical program and stored on secured servers with regular backup. Double data entry will be processed for 20% of the questionnaires to assess data quality. Furthermore, range checks for data values will be performed. Questionnaires will be stored in locked cabinets. Only the research team will have access to questionnaires and data.

The data are pseudonymized to ensure confidentiality. For this purpose, each study participant is assigned a research code. The code list (including name, date of birth, SAP research number, and contact data) is accessible only to the research member responsible for the assignment and data collection. It is stored locked on an external data carrier that is not accessible to the public or other team members.

The principal investigator will retain all collected data for at least 10 years. The code list will be destroyed at the end of the study.

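### The arm is fixed when the pre-numbered T0 pack goes out, before consent, although the protocol says randomisation follows consent and T0; the described mechanism does not ensure concealment

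*Protocol article*

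**What the plan says.** All references are to the protocol article.

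- **Timing as stated.** Randomization and allocation concealment opens by saying that dyads "will be randomly assigned to IG or CG after consent is given and initial questionnaires (T0) are completed".
- **How the list works.** A study-center member outside the study "created the randomization list with computer-generated random numbers linked to the research codes (i.e., a consecutive list of numbers"). The list is kept locked, and allocation is 1:1 in blocks of unstated size.
- **Where the code appears.** "Research codes are printed on the first questionnaires (T0"). From this the section concludes that "assignment based on the sequence of the list is determined by the time of receipt of the interest to participate" and, with it, by the handing out of the study papers.
- **When those papers go out.** Recruitment says that interested people receive the written information, a flyer, "the baseline set of questionnaires (T0), and an informed consent form (in person or delivered by mail").
- **Why concealment is claimed.** The staff who enrol, with the study coordinator given as the example, "will not release the randomization number until the signed consent form and baseline assessments have been completed".
- **Roles.** Under Blinding, analysts are unblinded and study team members each hold several tasks: "They are responsible for enrollment, data collection, management, and statistical analysis". Psycho-oncologists take no part in recruitment or data collection.

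**The concern.** One section gives two different moments of assignment, and they lie on opposite sides of consent. If the arm already belongs to the numbered pack, everything between handing out the pack and its return happens after assignment. That includes the decision to consent, the completion of T0 and any reminder from staff.

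This is harmless while nobody who influences that interval can know or guess the arm. The safeguard offered for this is that the enrolling person withholds the number. That protects the dyad from learning the arm early. It does not show that the enrolling person is kept from learning it.

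Selection bias is at stake. Participants cannot be blinded and the primary outcome is the self-reported GAD-7, so sound concealment is one of the few protections this design has. A coordinator who knew or suspected the arm could chase one dyad's paperwork harder than another's, and baseline adjustment for GAD-7 would not remove all of the resulting difference.

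**Working it through.** **1. Sequence of events, from the article's own statements**

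| Step | Event | Section |
|---|---|---|
| 1 | List made, linked to consecutive research codes | Randomization and allocation concealment |
| 2 | Codes printed on T0 | Randomization and allocation concealment |
| 3 | Interest shown; T0 and blank consent form handed over or mailed | Recruitment |
| 4 | Consent signed, T0 completed | Recruitment |
| 5 | Number released; IG relatives contacted, CG relatives not | Randomization and allocation concealment; Recruitment |

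Code determines list position, and list position determines arm. The code is attached at step 3, so the arm is fixed at step 3. The opening sentence of the randomisation section places assignment after step 4. Both cannot describe the same procedure. What happens after step 4 is disclosure of an assignment already made.

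**2. Who is kept from the key**

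Stated: the list's author is uninvolved, and the list is locked. Not stated: who may open it, or from whom the coordinator obtains the number to be released. Arms of enrolled dyads become visible at step 5, because only IG relatives are contacted.

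**3. How predictable the next arm could be**

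The article gives no figure on concealment to reproduce. Assume a fixed block size 2b known to the guesser, who always names the arm with more places left in the block. If every earlier arm in the block is known, the expected number of correct guesses per block is b + 2^(2b−1)/C(2b,b) − 1/2.

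- Blocks of 4 (b = 2): 2 + 8/6 − 0.5 = 2.833; 2.833/4 = 0.708.
- Blocks of 6 (b = 3): 3 + 32/20 − 0.5 = 4.1; 4.1/6 = 0.683.

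Full enumeration, with each earlier arm known independently with probability p, gives:

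| p | Blocks of 4 | Blocks of 6 |
|---|---|---|
| 1 | 0.708 | 0.683 |
| 0.5 | 0.599 | 0.584 |
| 0.25 | 0.554 | 0.548 |
| 0 | 0.500 | 0.500 |

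Packs still out or never returned leave earlier arms unknown, so p is below 1 in practice. Someone able to read the list needs no guess.

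**4. Imbalance from unreturned packs**

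Codes are used up at distribution. With return rate r (assumed, and unrelated to arm), 200 dyads need about 200/r codes. The variance of the arm difference is about (200/r) × r(1 − r) = 200(1 − r). The mean absolute difference is about 0.80 times the SD. Simulation with blocks of 4 agrees:

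| r | Codes | SD = √[200(1 − r)] | Mean absolute difference (simulated) | 95th percentile (simulated) |
|---|---|---|---|---|
| 0.8 | 250 | 6.3 | 5.1 | 12 |
| 0.6 | 333 | 8.9 | 7.1 | 18 |
| 0.4 | 500 | 11.0 | 8.8 | 22 |

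Effect on power: the article's sample size reproduces first. At d = 0.4, two-sided alpha 0.05 and 80% power, the t-test needs 99.08 per group, so 100 per group and 200 in total, with power 0.804. At 95/105 power is 0.803, and at 90/110 it is 0.800. A difference of 22 (89/111) gives 0.799.

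**The case against.** The strongest defence is that fixing an arm in advance does not unconceal it. Any pre-generated list, including sequential sealed envelopes, fixes arms before enrolment. Concealment depends on who can read the key, and here the list was made by an uninvolved person and locked away. This stands. A reader might infer that the code on T0 is itself the randomisation number, so that the number cannot be withheld and concealment has failed. The article does not support that: it says the random numbers are linked to the codes, it uses two separate terms, and a consecutive code shows no arm without the key.

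Other points also stand:

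- The restricted code list, "accessible only to the research member responsible for the assignment and data collection", holds names and contact data. It is the identity key and says nothing about access to arms.
- Packs follow the order in which interest is received, so nothing in the text lets staff choose a pack for a dyad. Uneven timing or chasing is what remains.
- The 71% and 68% figures need a known, fixed block size and every earlier arm known. They are not expected values.
- Imbalance unrelated to arm causes no bias and costs almost no power.
- Block size, and part of the access detail, may be in the full protocol, which a condensed article need not repeat.

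The defence does not remove the contradiction in timing, which is in the article's own words. Nor does it rescue the reason given for concealment, since withholding by the enrolling person does not conceal from that person.

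**Conclusion.** The point holds in this form: assignment is fixed at pack distribution, before consent, which contradicts the statement that randomisation follows consent and T0, and the mechanism described does not ensure concealment. The article does not show that concealment failed, or that enrolling staff can see the key. It leaves that access unstated while giving the enrolling coordinator the task of release, within a team that also collects and analyses the data unblinded.

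The size of any selection bias cannot be calculated from the document. Under assumed blocks of 4 or 6, prediction of the next arm lies between 50% and the ceilings of 71% and 68%; it is about 60% and 58% if half of the earlier arms are known. Imbalance is a side issue: even a difference of 22 dyads lowers power only from 0.804 to 0.799. The point should be corrected because the remedy is cheap and the outcome is self-reported in an open trial.

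**What to change.** For dyads still to be recruited:

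1. Use the research code on T0 for pseudonymisation only, without a link to the list.
2. Have the uninvolved list holder issue the next list entry only after signed consent and completed T0 have been logged.
3. State that enrolling staff have no access to the list.
4. Reword the randomisation section so that it gives one moment of assignment. Say how packs already distributed under the linked codes are handled.
5. Report the codes issued but not enrolled, by linked arm. For packs already issued this needs distribution records. It would show whether return differed between arms.

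The cost is one message per dyad to the existing list holder and an amendment to the randomisation text, which goes to the Ethics Committee like any other protocol change. Sample size and analysis are unaffected.

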#### Blinding

Blinding of participants and psycho-oncologists is not possible due to the active counseling intervention. However, psycho-oncologists are not involved in recruitment and data collection. Other care providers are blind to study participation and/or assignment. For organizational reasons, the analysts will not be blinded. The members of the study team will each take on several tasks. They are responsible for enrollment, data collection, management, and statistical analysis.

### Data collection, data management, confidentiality, and retention

Data will be assessed with patient questionnaires (paper–pencil), and medical data will be extracted from the medical record. The baseline set of questionnaires (T0) will be administered in person or delivered by mail. The follow-up questionnaires (T1) will be sent by mail with a prepaid envelope for return. Researchers will check the responses and, if necessary, contact nonresponders via telephone to promote complete follow-up.

All data will be transferred manually to a statistical program and stored on secured servers with regular backup. Double data entry will be processed for 20% of the questionnaires to assess data quality. Furthermore, range checks for data values will be performed. Questionnaires will be stored in locked cabinets. Only the research team will have access to questionnaires and data.

The data are pseudonymized to ensure confidentiality. For this purpose, each study participant is assigned a research code. The code list (including name, date of birth, SAP research number, and contact data) is accessible only to the research member responsible for the assignment and data collection. It is stored locked on an external data carrier that is not accessible to the public or other team members.

The principal investigator will retain all collected data for at least 10 years. The code list will be destroyed at the end of the study.

### Statistical analysis

Statistical analysis will be performed using IBM SPSS Statistics for Windows. Missing data in accordance with missing completely at random (MCAR) or missing at random (MAR) assumptions will be imputed using a multiple imputation procedure. In addition, missing values due to drop-out or data not missing at random (NMAR) will be analyzed by pair-wise deletion.

Descriptive analyses will be performed concerning socio-demographic and medical data.

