## Methods/design

### Trial design

The study is a single-center, prospective, randomized controlled trial (RCT) with two measurement time points. Relatives of lung cancer patients and, thus, the patients themselves (i.e., dyads) are randomly assigned to the CALM intervention group (IG) or the control group (CG) regardless of their disease or treatment stage. The relatives in the IG will receive psycho-oncological support according to the CALM manual, whereas the relatives in the CG will receive usual psycho-oncological treatment (usual care). However, the patients in both study arms will not get a specific intervention. The relatives and the patients complete the assessments at baseline (T0) and after the intervention (IG, T1) or after 6 weeks (CG, T1). Figure 1 shows the study workflow, and Table 1 shows the SPIRIT reporting guideline schedule.

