#### Main research question

The primary and secondary endpoints will be analyzed according to the intention-to-treat principle. Treatment effects (between-group effects) in primary and secondary outcomes will be evaluated using analysis of covariance (ANCOVA) adjusting for baseline values. Statistical significance (*p* < 0.05, two-sided) and effect sizes (*ή*^2^) will be reported for all between-group differences [27]. In addition, within-group effects, including standardized effect sizes (SES) and accompanying 95% confidence intervals (CIs), will be calculated for both study groups.

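### Drop-outs are assigned to pair-wise deletion, which turns an analysis called intention-to-treat into a completers' analysis and overlaps with the plan's own imputation rule

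*Protocol article*

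**What the plan says.** Under Statistical analysis, the protocol article divides missing data into two classes. Values that are MCAR or meet "missing at random (MAR) assumptions will be imputed using a multiple imputation procedure". For the rest, "missing values due to drop-out or data not missing at random (NMAR) will be analyzed by pair-wise deletion".

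Under Main research question, "The primary and secondary endpoints will be analyzed according to the intention-to-treat principle", and treatment effects "will be evaluated using analysis of covariance (ANCOVA) adjusting for baseline values".

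Three other statements bear on this:

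- Trial design describes a "randomized controlled trial (RCT) with two measurement time points".
- Randomization and allocation concealment says that dyads "will be randomly assigned to IG or CG after consent is given and initial questionnaires (T0) are completed".
- Blinding says: "For organizational reasons, the analysts will not be blinded".

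**The concern.** A relative who drops out after randomisation has a T0 GAD-7 and no T1 GAD-7. One section removes that person; the next promises an analysis by randomised group with nobody set aside. Both cannot hold for the primary endpoint.

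The split itself is also unsound, for three reasons:

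- Deletion is assigned to NMAR, the class in which it can distort the comparison. Imputation is kept for the classes in which baseline-adjusted deletion does little harm.
- Drop-out is a reason for a missing value, whereas MAR and NMAR are assumptions about the mechanism. A drop-out whose loss is MAR falls under both rules.
- Observed data cannot separate MAR from NMAR. Whoever applies the split makes a judgement, and here the analysts know the allocation.

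At stake are the primary estimate and its label. The same endpoint feeds the interim analysis at n = 88, where closing or continuing turns on effects of 0.4 and 0.6, only 0.2 apart.

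**Working it through.** **1. The plan's own figure.** Inputs from Sample size calculation: d = 0.4, "at a significance level of alpha = 0.05 and beta = 0.2 for comparing two independent samples". The test is two-sided (Main research question).

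n per group = 2(z₀.₉₇₅ + z₀.₈₀)²/d² = 2(1.960 + 0.842)²/0.16 ≈ 98.1, so 99. The t-test version gives 99.1, rounded up to 100. The stated 200 reproduces; it is the number to be analysed, and the article states no allowance for loss.

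**2. What deletion does here.** The model has one outcome (T1) and one baseline covariate (T0). Randomisation follows T0, so a randomised relative should have the covariate. Pair-wise deletion then drops everyone without T1, which is a complete-case analysis.

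**3. When deletion biases the estimate.** Simulation of baseline-adjusted regression on completers, true d = 0.4, assumed T0–T1 correlation 0.5, assumed log-odds slope of 1 per SD for loss:

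| Mechanism | Loss CG/IG | Estimated d |
|---|---|---|
| MCAR | 20%/20% | 0.40 |
| MAR given T0 | 20%/20% | 0.40 |
| NMAR, same in both arms | 20%/20% | 0.40 |
| NMAR, same in both arms | 10%/30% | 0.53 |
| NMAR in IG only | 20%/20% | 0.53 |

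Bias needs a difference between arms in the loss or in its mechanism.

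**4. Size in one concrete case.** Assumed: no true effect, 25% loss in IG and 15% in CG, correlation 0.5, logistic loss rising with T1 anxiety. The last column imputes T1 under MAR from arm and T0 only.

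| Mechanism | Slope per SD | Unadjusted completers | Planned ANCOVA | MAR imputation |
|---|---|---|---|---|
| Same in both arms | 0.5 | 0.048 | 0.036 | 0.036 |
| Same in both arms | 1.0 | 0.080 | 0.063 | 0.064 |
| Informative in IG only | 0.5 | 0.118 | 0.090 | 0.090 |
| Informative in IG only | 1.0 | 0.213 | 0.162 | 0.164 |

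Simulation runs differ slightly, so the planned-ANCOVA ranges are given as about 0.03–0.06 and 0.09–0.17 SD. As a share of the planned effect, the IG-only case is 0.090/0.4 = 22.5% to 0.162/0.4 = 40.5%. With the same mechanism and 20% loss in each arm, the result is zero to two decimals. At a correlation of 0.7 the IG-only figures fall to about 0.06–0.11.

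**5. Power.** Power ≈ Φ(d√(n/2) − 1.960). With 100 per group, Φ(2.828 − 1.960) = 0.807. If 20% are deleted (80 per group), Φ(2.530 − 1.960) = 0.716. The 20% is again an assumption.

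**The case against.** The strongest reply has five parts.

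- **The planned model already protects against MAR loss given T0.** This stands. Completers' ANCOVA is unbiased in that case, and unadjusted means (0.05–0.08 and 0.12–0.21 SD) overstate the problem because they are not the planned analysis.
- **MAR imputation does not remove the illustrated bias.** This also stands. From arm and T0 alone it gives nearly the same figures as deletion. It can gain only through auxiliary variables, and drop-outs will have few or no T1 scales of their own to supply them. NMAR has to be handled by a sensitivity analysis, which shows how far the result depends on the assumption but does not remove the bias.
- **Differential loss is not shown.** A reader might infer it from the statement under Recruitment that control relatives are not actively contacted. That statement concerns counselling appointments. T1 collection (mailed forms, prepaid return, telephone contact of non-responders) is described without distinction by arm, and stopping sessions is not the same as missing T1. Outcome-related discontinuation is foreseen under Monitoring: harms, so differential loss remains possible, but the article does not establish it.
- **An article may leave the sensitivity analyses and the definition of drop-out to a fuller document.** Agreed; their absence is not the point. The point is a rule that is stated and that conflicts with the stated principle.
- **The deletion sentence opens with words that could signal a supplementary analysis.** This is a weak reading: the sentence assigns a method to a class of missing values, and no other method is named for drop-outs.

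**Conclusion.** The conflict is in the text and does not depend on any simulation: deleting drop-outs by rule gives a completers' analysis, not the intention-to-treat analysis that is promised. The two missing-data rules also overlap, and unblinded analysts are left to choose between them on grounds that the data cannot settle.

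The size of any bias is conditional. Under the assumed 25%/15% loss, correlation of 0.5 and slopes of 0.5–1.0, the planned ANCOVA would show a spurious benefit of about 0.03–0.06 SD with a common mechanism and 0.09–0.17 SD with informative loss in IG only. It would show about none if loss and mechanism were equal.

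A reader might infer that deletion under NMAR is always biased, or that this trial's estimate will be. The documents support neither: they give no drop-out rate and no evidence of a difference between arms. How many relatives would be deleted is also unknown, since incomplete items on returned forms could still fall under the imputation rule.

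**What to change.** Replace the pair-wise deletion sentence with the following:

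1. All randomised relatives stay in the primary analysis. Missing T1 scores, including those of drop-outs, are multiply imputed under MAR, using arm, T0 GAD-7 and auxiliary variables already collected: the other T0 scales, the patient's T0 and T1 scores, UICC stage and number of sessions.
2. NMAR is addressed by a delta-adjusted (tipping-point) sensitivity analysis, with the shift varied separately by arm. The text should say plainly that MAR imputation alone does not remove NMAR bias.
3. The completers' ANCOVA is reported as a sensitivity analysis only.

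The cost is a change of wording and some additional analysis, with no new data. The change should be made before the final analysis and, if it has not yet been run, before the interim analysis.
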